### 2.4 Data management

Data management will comply with the requirements of the General Data Protection Regulation (2018). Personal data will be pseudonymised, with the master list linking participant identification numbers to personal information stored securely and separately from other data in a locked office within the School of Nursing and Midwifery, Queen’s University Belfast. A pseudonymised case report form (CRF) will serve as a consolidated resource documenting the data collected from each participant, with access limited to authorised individuals from the central research team at Queen’s University Belfast. These individuals will be responsible for data entry and validation at the point of entry into the CRF. Data from collaborating sites (*i.e.,* information from patient medical records) will be sent to the central research team via encrypted emails containing pseudonymised, password-protected data collection forms. Transcripts of audio-recordings will be pseudonymised, with transcription undertaken by a specialist service who has completed a data sharing and confidentiality agreement. All audio-recordings will be destroyed after the transcripts have been checked for accuracy. All paper data will be stored in a Master File and Site Files held within locked offices at the School of Nursing and Midwifery, Queen’s University Belfast and across the collaborating centres, respectively. All electronic data will be password protected and stored on an encrypted and password protected computer, inside a locked office at the School of Nursing and Midwifery, Queen’s University Belfast. On request, access to data will be granted for authorised representatives of the sponsor (Queen’s University Belfast) and regulatory authorities to facilitate study-related monitoring, audits, and inspections.

### 2.5 Data analysis

#### 2.5.1 Quantitative data.

Quantitative data analysis will be managed on Statistical Package for the Social Sciences (IBM SPSS Statistics, Version 31). Continuous data will be presented as mean ± standard deviation, with discrete data reported as absolute numbers and percentages. Categorical data will be displayed as frequency/ percentages. For participant outcomes, repeated measures analysis of variance will be used to investigate the effect of time point on outcome scores. Due to the absence of statistical power, the results will be used to identify preliminary evidence of promise for the intervention across different participant outcomes, with potential effect sizes generated to inform the required sample size for a future definitive evaluation.

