#### 2.2.4 Carers.

The target population of HELP is informal carers of patients with symptomatic HF. These individuals will be eligible to participate if they are: 1) Aged 18 years or older; 2) Physically and mentally capable of operating a digital device; 3) Able to engage comfortably in conversation with peers and capable of reading written materials; 4) Caring (regular, unpaid care) for a person with a clinical diagnosis of HF who is receiving standard evidence-based HF therapies and has either HF symptoms or one episode of decompensation (symptoms requiring medical attention) in previous six months; and 5) Capable of speaking and understanding English.

There will be five programme rollouts of HELP (six weeks each) across each of the three collaborating nations over a one-year period, with twelve carers per rollout (60 carers per nation; 180 carers in total). This sample size was pragmatically determined by the maximum study duration within the funding limit, along with the recruitment rate demonstrated in the pilot study [10].

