#### 2.2.8 Intervention design.

HELP design was based on prior literature and comprehensive input from carers of patients with HF and healthcare professionals, with the co-development and feasibility testing of this intervention previously reported in detail [10]. HELP constitutes a six-week, nurse-led, psychoeducational programme comprising two components:

1)
*Online support group sessions*

Nurse-led, weekly online support group sessions are delivered to groups of approximately twelve carers over a six-week period. Each session lasts sixty minutes and is underpinned by a standardised, educational presentation covering the topics displayed in Table 1. Following each educational presentation, the HF nurse facilitates a group discussion to issue tailored advice, guidance, and signposting, along with providing a platform for carers to engage in peer support.

**Table 1 pone.0347037.t001:** Support Group Schedule.

Session Number	Topic	Content
1	Introduction	Group introductions Summary of HELP content Guidance on access and usage of self-directed educational resources (booklet and website)
2	Understanding HF	Overview of HF Symptoms Prognosis Palliative care
3	Personal Wellbeing	Looking after physical and emotional wellbeing Management strategies for complex emotions
4	Communication and Support	Communicating with loved ones and healthcare professionals
5	Practical Skills for Supporting Self-Management	Controlling diet and salt intake Management of fluid and medication Exercise Monitoring symptoms at home
6	Feedback	Discussion of experience and final comments/ questions Feedback on HELP and areas of improvement

**Legend** HELP = HEart faiLure carer support Programme and HF = heart failure.

2)
*Self-directed, educational resources (booklet and website)*

Upon HELP enrolment, carers will receive an educational booklet (S3 Text) and access to a supplementary website. Both resources were co-designed and professionally produced. The educational booklet complements the online support group sessions by facilitating self-directed learning across the following five chapters:

Chapter 1: What is HF?Chapter 2: Planning for the futureChapter 3: Looking after yourselfChapter 4: CommunicationChapter 5: Your role as a carer

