#### 2.2.9 Intervention delivery.

HELP will be delivered by local specialist HF nurses across the collaborating sites. Following recruitment, carers will be assigned a start date for HELP. One week prior to the first online support group session, carers will receive the educational booklet and access to the supplementary website, along with supporting programme materials (*i.e.,* online support group schedule and guidance on joining online sessions). Carers will be advised to read each chapter of the educational booklet and supplementary website before the corresponding online support group session. The online support group sessions will run on ‘Zoom’, with a link and password to each session issued to carers before commencement. Carers will receive a reminder email two days before each online support group session. The research team will remain in contact with all participants to provide ongoing support with accessing the online support group sessions and supplementary website.

The nurse-led, online support group sessions will be delivered using an informal approach to facilitate a comfortable environment for the carers. Each session will consist of twelve carers and last approximately sixty minutes. The sessions will initiate with a standardised, educational presentation (approximately 20 minutes) on the allocated topic, with the remainder of the session (approximately 40 minutes) dedicated to questions raised during the session or submitted via the website; group discussion; tailored advice and signposting; and peer support. Carers will receive the option of having their cameras switched on or off during the sessions and will be encouraged to use the chat function to ask questions if unwilling to speak in front of the group.

Five programme rollouts of HELP (six weeks each) will be delivered across each of the three collaborating nations over a year period, with twelve carers per rollout (60 carers per nation; 180 carers in total). Rollouts will be separated by four-week windows, which will account for staff holidays and provide recruitment intervals for the subsequent rollout.

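### The named repeated measures ANOVA takes 180 carers as independent although HELP runs in 15 groups of about twelve; if change is correlated within groups, its standard errors are too small

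*Protocol article*

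**What the plan says.** Section 2.5.1 names the method for participant outcomes: "For participant outcomes, repeated measures analysis of variance will be used to investigate the effect of time point on outcome scores". It mentions no term for group, nurse, site or nation. It adds that the study lacks statistical power, that the results will be read as preliminary signs of promise, and that the resulting effect sizes will inform the sample size of a later definitive evaluation.

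Delivery is by group. Section 2.2.8: "Nurse-led, weekly online support group sessions are delivered to groups of approximately twelve carers over a six-week period". Section 2.2.4 sets the number of rollouts: "There will be five programme rollouts of HELP (six weeks each) across each of the three collaborating nations over a one-year period". The group size given there is twelve, which makes 60 carers in each nation and 180 overall. Section 2.2.9 repeats the group size ("Each session will consist of twelve carers and last approximately sixty minutes") and places each carer in a rollout: "Following recruitment, carers will be assigned a start date for HELP". About 40 of each session's 60 minutes go to carers' questions and to "group discussion; tailored advice and signposting; and peer support".

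**The concern.** Repeated measures ANOVA with time as its only factor handles the correlation between one carer's repeated scores. It takes the changes of different carers as independent. Carers in one rollout share a nurse, six weekly sessions and the same peers. Section 2.2.8 also gives support from peers and professionals as one route by which HELP is meant to relieve stress and burden. If the programme works partly through the group, some groups will improve more than others, and that variation belongs in the error term for mean change. The named analysis leaves it out.

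Two things are at stake. The precision shown behind any sign of promise would be overstated. And the effect sizes would go into the next sample size calculation without the ICC that a group-delivered programme needs, because the named analysis does not produce one.

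**Working it through.** **The plan's own figure.** 5 rollouts × 3 nations = 15 groups; 15 × 12 = 180 carers. This reproduces the stated total. There is no power calculation to reproduce, since section 2.2.4 sets the sample size pragmatically.

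**Inputs.** Group size m = 12 and N = 180 (2.2.4, 2.2.9). Three time points: baseline, week six, six months post-intervention (2.3.4). Assumed, because the article does not give them: an ICC of change (ρ) of 0.01 to 0.10, and a two-sided 5% test.

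**Formulas for mean change.**
- Design effect: DE = 1 + (m − 1)ρ = 1 + 11ρ
- Effective sample: 180 / DE
- True SE relative to naive SE: √DE; shortfall of the naive SE: 1 − 1/√DE
- Actual error of a nominal 5% test: 2[1 − Φ(1.96/√DE)]

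| ICC of change | DE | Effective n | True / naive SE | Naive SE too small by | Actual error |
|---|---|---|---|---|---|
| 0 | 1.00 | 180 | 1.00 | 0% | 5.0% |
| 0.01 | 1.11 | 162 | 1.05 | 5% | 6.3% |
| 0.05 | 1.55 | 116 | 1.24 | 20% | 11.5% |
| 0.10 | 2.10 | 86 | 1.45 | 31% | 17.6% |

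At ρ = 0.10, for example: DE = 1 + 11 × 0.10 = 2.10; √2.10 = 1.449; 1 − 1/1.449 = 0.31; 1.96/1.449 = 1.353, which gives 17.6%.

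**Check by simulation.** A three-time-point repeated measures ANOVA was run on 15 × 12 simulated carers with no true time effect, 6,000 runs per scenario. Two patterns of group-by-time variation were used: one shift per group shared by both post-baseline visits, and independent group deviations at each visit.

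| Scenario | Rejection at nominal 5% (shared shift to independent deviations) |
|---|---|
| No group effect | 4.9% |
| Group effect constant over time | 5.2% |
| ICC of change 0.01 | 6.1% to 6.7% |
| ICC of change 0.05 | 11.3% to 14.3% |
| ICC of change 0.10 | 17.7% to 25.0% |

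The second row matters: a stable difference between groups cancels in within-person change and causes no inflation. Only group-by-time variation does. The same ANOVA run on the 15 group means stayed between 4.9% and 6.2% throughout.

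**How well the ICC could be estimated.** With 15 groups of 12, F = (1 + 11ρ)/(1 − ρ) on 14 and 165 degrees of freedom. An estimate of 0.05 gives F = 1.63 and a 95% interval from 0 (lower limit truncated) to about 0.21. An estimate of 0.01 gives 0 to about 0.13. The ICC is estimable, but imprecisely.

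**The case against.** The strongest reply is that these outcomes carry little inferential weight. The third of three objectives is only to explore impact, the article disclaims power and definitive findings (2.5.1, 3.1), and it states no alpha, primary hypothesis or success threshold. A reader might infer that interventions will be declared promising too often at a known rate. The documents do not support that, because they contain no significance rule to which such a rate could attach. This part of the reply stands and lowers the severity. It does not remove the point: low power concerns missed effects, whereas ignored clustering makes estimates look more precise than they are.

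The size is also unknown. A reader might infer that sharing a group makes the standard errors wrong by construction. The documents do not show that: they give no ICC, and at an ICC of change of zero nothing is wrong. The statement must stay conditional.

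Nor is the ICC lost. Each carer's rollout follows from the assigned start date, so it can be computed from the data collected. It is simply not part of the named analysis.

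That this is a condensed article, with no analysis plan shown, is a fair caution about the details of a random-effects structure. It does not cover the point itself, since the article names a specific method and that method does not allow for groups.

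Two smaller reservations also stand. Fixed group membership is inferred from start dates and six-week rollouts rather than stated, and section 2.2.8 makes the group size approximate. Patients do not attend the sessions and their enrolment is optional, so any effect on patient outcomes is less certain.

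**Conclusion.** The point holds in conditional form. The analysis named in section 2.5.1 does not allow for the 15 delivery groups. If change is correlated within groups, which the delivery model makes plausible, the standard errors and any intervals or p-values for carer change will be too optimistic. Under the assumed ICC of change of 0.01 to 0.10, the true standard error is 5% to 45% larger than the naive one, which is the same as saying that the naive one is 5% to 31% too small. With an assumed two-sided 5% test, the actual error is about 6% to 18% for mean change and up to about 25% for the three-time-point test. The estimated mean changes are not biased by the grouping. Because the outcomes are exploratory, this is a matter that should be fixed rather than one on which the study depends.

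**What to change.** Record the rollout group for every carer. Replace the repeated measures ANOVA with a linear mixed model (MIXED in SPSS, the software already named) containing fixed time, a random carer intercept and a random group-by-time term, with Satterthwaite or Kenward-Roger degrees of freedom. The group-by-time term is the essential part, since a group intercept alone does not address correlated change. Group-level or cluster-robust inference with a small-sample correction for 15 groups would also do. Fixed effects for nation and rollout number are optional.

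Report the ICC of change with its interval, which will be wide, beside the effect sizes meant for the future sample size.

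The cost is revised wording, a group identifier and a little analysis time. Recruitment, sample size and the outcome schedule are unchanged. The downside is somewhat wider intervals.

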#### 2.3.4 Participant outcomes.

The short and long-term impact of HELP on outcomes for carers and patients will be assessed across data from validated questionnaires, patient diaries, and medical records (see Table 2). Participant outcome data will be collected at three time points: 1. Baseline, 2. Post-intervention (week six), and 3. Six months post-intervention.

**Table 2 pone.0347037.t002:** Participant Outcomes and Measurement Instruments.

Sample	Outcome	Measurement Instrument	Time Point		
			Baseline	Post-Intervention (Week 6)	6 Months Post-Intervention
**Carers**	Carer Burden	Zarit Burden Interview, Short Form [26]	X	X	X
	Carer Preparedness	Preparedness for Caregiving Scale [27]	X	X	X
	QoL	12-Item Short Form Survey [28]	X	X	X
	Anxiety and Depression	Hospital Anxiety and Depression Scale [29]	X	X	X
	Stress	Perceived Stress Scale [30]	X	X	X
	Social Support	Multidimensional Scale of Perceived Social Support [31]	X	X	X
**Patients with HF**	Disease-specific, QoL	Minnesota Living with HF Questionnaire [32]	X	X	X
	Generic, QoL	EuroQoL Five Dimension Questionnaire [33]	X	X	X
	GP Visits with Reasons over Previous 6 Months	Bespoke, Recall Questionnaire at Baseline and Patient Diary Self-Completed from Baseline to 6 Months	X		X
	Most Recent LVEF Measurement	Medical Record	X		X
	Hospital Admissions with Reasons over Previous 6 Months	Medical Record	X		X

**Legend** QoL = Quality of Life; HF = Heart Failure; GP = General Practitioner; and LVEF = Left Ventricular Ejection Fraction.

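### GP visits and hospital admissions, two event counts, fall under a repeated measures ANOVA of scores, which gives no rate ratio with a confidence interval and ignores observed time (minor)

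*Protocol article*

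**What the plan says.** Section 2.3.4 of the protocol article treats diary and medical-record data as participant outcomes alongside the questionnaires. Among the patient outcomes, Table 2 lists "GP Visits with Reasons over Previous 6 Months" (a recall questionnaire at baseline, then a self-completed diary) and "Hospital Admissions with Reasons over Previous 6 Months" (medical record). Both are marked at baseline and six months post-intervention only, not at week six.

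Section 2.5.1 names one inferential method: "For participant outcomes, repeated measures analysis of variance will be used to investigate the effect of time point on outcome scores". No count or rate method appears. The descriptive summaries are mean ± standard deviation for continuous data, "with discrete data reported as absolute numbers and percentages", and frequencies and percentages for categorical data.

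On use of the findings, the section opens with "Due to the absence of statistical power" and continues that "the results will be used to identify preliminary evidence of promise for the intervention across different participant outcomes". A second purpose, planning the later study, follows in the same sentence: "with potential effect sizes generated to inform the required sample size for a future definitive evaluation". The section does not say what kind of effect size is meant, and it sets no threshold for promise.

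**The concern.** The method is written for scores, but the class of outcomes it is applied to contains two event counts. Counts of admissions and visits are naturally summarised as events per unit of observed time and compared as a ratio. A repeated measures ANOVA compares mean raw counts and treats every patient's period as the same length.

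Two things are at stake. First, the article wants effect sizes for planning a definitive study, and its Discussion names fewer readmissions as a possible benefit to patients. To size a comparison of admission rates one wants a baseline rate, a rate ratio with its uncertainty, and a dispersion. Second, Table 2 has the diary running from baseline, whereas the time point is six months after a six-week programme. Some patients may also be followed only in part. A raw count cannot adjust for either.

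**Working it through.** **1. Inputs from the article.** Patients: about 180, one per carer, where carers = 5 rollouts × 3 nations × 12 = 180. This reproduces the stated total. The two counts have two time points each. The article gives no admission rate, visit rate, share of zeros, dropout, alpha or power, so there is no power figure to reproduce.

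**2. What the method becomes.** With two time points and D = follow-up count − baseline count, the ANOVA F equals t², where t = mean(D) / (SD(D)/√n). The quantity estimated is the difference in mean counts, μ₂ − μ₁. A rate model estimates (μ₂/T₂)/(μ₁/T₁), where T is observed time.

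**3. Is the test itself harmed?** Overdispersed (gamma-Poisson) counts were simulated with 3,000 replicates and two-sided 5% tests. All of these settings are assumptions: baseline mean 0.2, 0.3 or 0.5 admissions per six months; dispersion parameter k = 0.5 or 1; patient effects shared or independent between periods; equal, complete periods. A mean of 2 was used for GP visits. The comparator was the log ratio of means with a within-patient robust standard error.

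| Setting | ANOVA | Rate ratio |
|---|---|---|
| Admissions halved, n = 180 | 57–97% | 58–97% |
| Admissions down 30%, n = 180 | 22–58% | 22–59% |

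With no true change, the ANOVA rejected in 4.4% to 5.7% of runs for n = 120 to 180. With a mean of 2 GP visits, it detected a halving in 97% to 100% of runs at n = 180. The gain in power from the rate analysis is about 0 to 2 percentage points.

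**4. What is carried into planning.** Take admissions falling from 0.2 to 0.1 with k = 1 (assumed). For a two-arm study at 80% power and two-sided 5%, n per arm = 2 × (1.960 + 0.842)² / d² = 15.70 / d².
- Negative binomial rate formula: 7.849 × (1/0.2 + 1/0.1 + 2/1) / (ln 0.5)² = 7.849 × 17 / 0.4805 ≈ 278 per arm.
- Effect on the SD of raw counts: the variances are 0.2 + 0.04 = 0.24 and 0.1 + 0.01 = 0.11, averaging 0.175. Then d = 0.1/√0.175 = 0.239, giving 275 per arm.
- Effect on the SD of change, independent patient effects: d = 0.1/√(0.24 + 0.11) = 0.169, giving 550 per arm.
- Effect on the SD of change, shared patient effects: d = 0.1/√(0.3 + 0.01) = 0.180, giving 487 per arm.

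So one standardisation reproduces the rate-based size and the other roughly doubles it. The article does not say which effect size it will use.

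**5. Observed time.** The baseline window is six months, about 26 weeks. If the diary is counted from baseline to six months post-intervention, follow-up is about 6 + 26 = 32 weeks, and 32/26 = 1.23. An unchanged visit rate would then give a mean raw count 23% higher. A true fall of 1 − 26/32 = 19% would show as no change. If the count is cut to the previous six months, as the row label suggests, the ratio is 1.00. The effect therefore lies between none and about 23%, before any incomplete follow-up.

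**The case against.** The strongest reply is that the ANOVA sentence concerns scores, that discrete data have their own descriptive summary, and that an article may leave the model for two counts to a fuller plan. This has some force. But the sentence opens with participant outcomes as a class, and Table 2 puts the counts in that class, so a method has been named and it fits them poorly.

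It is also fair that a reader could derive much of what is wanted. With equal six-month windows the mean count is the rate per period, the ratio of two means is a crude rate ratio, and k can be estimated as mean²/(SD² − mean). What would be missing is a confidence interval for the ratio and any adjustment for observed time.

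Stronger readings are tempting but unsupported:
- A reader might infer that both counts are mostly zero. The article gives no rates. At the assumed admission means, 67% to 85% of patients have none. At an assumed mean of 2 GP visits only 33% to 45% do, and these patients are symptomatic or recently decompensated.
- A reader might infer that a large fall in admissions would look like no promise. The ANOVA detects it about as often as a rate analysis, and low event numbers limit both.
- A reader might infer that the counts would rank last. The article never says that its effect sizes are standardised, and it describes no ranking of outcomes by effect size.

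**Conclusion.** The point holds as a minor one. As written, the only inferential method for GP visits and admissions is a paired comparison of mean raw counts. Under the assumed rates this costs nothing material in type I error or power. What is lost is a directly usable estimate: a rate ratio with its interval, a dispersion, and an allowance for observed time that could matter by up to about 23% for GP visits, depending on how the diary period is read.

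The weight is limited further because these are two of eleven outcomes in Table 2, the study is mainly about implementation, and the article itself disclaims power and definitive findings. The simulated figures rest on assumed rates, dispersion and equal windows. The planning figures in step 4 also depend on an effect-size metric that the article leaves open, and the choice between the SD of change and the raw SD affects questionnaire scores as well.

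**What to change.** In section 2.5.1, limit repeated measures ANOVA to the continuous outcomes, such as the questionnaire scores. Add a sentence that GP visits and hospital admissions will be analysed with a log-link count model (negative binomial, or Poisson GEE with robust standard errors), clustered on patient, with the log of observed time as offset. Report the rate per period, the rate ratio with 95% CI and the dispersion, and carry these forward to the later study.

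State the start and end of the follow-up window for each count, so that the diary period and the six-month post-intervention time point agree.

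The cost is one routine model and a sentence or two of text. No new outcome data are needed, only the dates between which each patient was observed.

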### 1.2 Objectives

1)Evaluate the multi-faceted implementation strategy via a process evaluation of acceptability, fidelity, and context of HELP delivery across real-world clinical sites.2)Estimate the economic cost of HELP implementation.3)Explore the short and long-term impact of HELP on outcomes for carers and patients.

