#### 2.2.5 Patients.

Patients who are receiving informal support from the recruited carers will be invited to participate via the provision of data, which will allow their perspectives on HELP implementation to be captured, whilst also facilitating an assessment of the potential, dyadic impact of the intervention. These patients will be eligible to participate if they are: 1) Aged 18 years or older; 2) Physically and mentally able to engage comfortably in conversation and capable of reading written materials; 3) Clinically diagnosed with HF and receiving standard evidence-based HF therapies and either have HF symptoms or one episode of decompensation (symptoms requiring medical attention) in previous six months; 4) Able to speak and understand English; and 5) Receiving regular, unpaid support with managing their condition from a loved one (*i.e.,* a relative or spouse) or friend. Patients will be ineligible if their carers refused to participate in HELP. Carers will remain eligible for participation regardless of patient enrolment. One patient per carer will be invited to participate to enhance sample diversity (approximately 180 patients in total).

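### Repeated measures ANOVA, as fixed for participant outcomes, discards observed week-6 scores of anyone missing another assessment; an all-available-data mixed model with two named baseline contrasts would serve Objective 3 better

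*Protocol article*

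**What the plan says.** Section 1.2, Objective 3, is to "Explore the short and long-term impact of HELP on outcomes for carers and patients". Section 2.3.4 repeats this aim ("The short and long-term impact of HELP on outcomes for carers and patients will be assessed") and sets the schedule: "Participant outcome data will be collected at three time points: 1. Baseline, 2. Post-intervention (week six), and 3. Six months post-intervention". In Table 2 every carer scale, the Minnesota questionnaire and the EuroQoL questionnaire are collected at all three points. GP visits, LVEF and hospital admissions are collected at baseline and 6 months only.

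Section 2.5.1 gives the analysis: "repeated measures analysis of variance will be used to investigate the effect of time point on outcome scores", in SPSS Version 31. No other inferential method and no comparison with baseline is named. The same section says that power is absent, that results are preliminary, and that the effect sizes will help to size a later definitive study.

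The planned sample is 180 carers and about 180 patients. On its basis, section 2.2.4 says: "This sample size was pragmatically determined by the maximum study duration within the funding limit", together with the pilot's recruitment rate. Section 2.2.2 provides for logging reasons for withdrawal. No attrition rate is given. Section 3.1 lists the non-randomised design and lack of power as limitations, but not attrition.

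**The concern.** The method named and the question asked do not fit each other well, for two reasons.

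First, conventional repeated measures ANOVA works on complete rows. A participant who returns the baseline and week-6 questionnaires but not the 6-month one contributes nothing, even to the change from baseline to week 6. The short-term result would normally have the better retention, yet it inherits the losses of the long-term one.

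Second, the stated target is the overall effect of time across three points. Objective 3 needs two separate quantities: the change to week 6 and the change to 6 months. An overall test can be significant whether a benefit lasts or has faded by 6 months.

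At stake are the precision of the before–after changes and, if those who drop out differ in their scores, the effect sizes that are to be carried into the next study.

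**Working it through.** **Sample size (section 2.2.4).** 5 rollouts × 12 carers × 3 nations = 180, which agrees with the article. There is no power calculation to reproduce.

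**Data discarded.** The article gives no missing-data rates, so these are assumptions: 10% at week 6 with 20% at 6 months, and 20% with 30%. Baseline is taken as complete. Two patterns bracket the result:

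- Monotone: everyone missing at week 6 is also missing at 6 months. Complete rows = 180 × (1 − 6-month rate).
- Independent: complete rows = 180 × (1 − week-6 rate) × (1 − 6-month rate).

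Share of week-6 data discarded = (week-6 available − complete) / week-6 available.

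| Missing at week 6 / 6 months | Week-6 available | Complete, monotone | Discarded | Complete, independent | Discarded |
|---|---|---|---|---|---|
| 10% / 20% | 162 | 144 | 18/162 = 11% | 129.6 | 32.4/162 = 20% |
| 20% / 30% | 144 | 126 | 18/144 = 12.5% | 100.8 | 43.2/144 = 30% |

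The monotone figure depends on how the two rates are paired. With 10% and 30% it is (162 − 126)/162 = 22%; with 20% at both points it is zero. The independent figure always equals the 6-month rate.

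**Precision.** For a simple paired week-6 change, the standard error grows by √(available/complete): √(162/144) = 1.06 and √(144/126) = 1.07 if monotone; √(162/129.6) = 1.12 and √(144/100.8) = 1.20 if independent.

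**Bias.** A simulation of 400,000 participants assumed three visits, SD 1, correlation 0.6 and a true change of −0.30 SD at both follow-ups (lower is better). Week 6 was complete, and 6-month dropout depended on the week-6 score, with a log-odds slope per SD as shown.

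| Missing at 6 months | Slope | Week-6 change, completers | Week-6 change, all data | 6-month change, completers |
|---|---|---|---|---|
| 20% | 0 | −0.300 | −0.300 | −0.301 |
| 20% | 0.5 | −0.338 | −0.300 | −0.301 |
| 20% | 1.0 | −0.370 | −0.300 | −0.301 |
| 30% | 0 | −0.300 | −0.300 | −0.301 |
| 30% | 0.5 | −0.358 | −0.300 | −0.303 |
| 30% | 1.0 | −0.401 | −0.300 | −0.302 |

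In this scenario, score-related dropout overstates the week-6 change by about 0.04 to 0.10 SD. A likelihood-type estimate using all available data does not, at either time point. The 6-month completer estimate is unaffected here, and with slope 0 there is no bias at all.

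**What the overall test shows.** One simulated data set of 144 completers had a true benefit at week 6 and none at 6 months. The time effect was F(2, 286) = 7.23, p = 0.0009. The contrasts with baseline were −0.25 (p = 0.001) at week 6 and −0.001 (p = 0.98) at 6 months. The overall test alone does not reveal that the benefit had gone; the contrasts, computed from the same data, do.

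**The case against.** The outcome analysis is exploratory and belongs to an uncontrolled implementation study, and the article says that its results are not definitive. Imputation before the ANOVA would be compatible with the text, and missing-data rules and contrasts may stand in a fuller plan. All of this is fair and limits the weight of the point. It does not remove it: the article has already chosen the model, and the effect sizes from it have a declared further use.

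Four stronger readings are tempting but not supported:

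- A reader might infer that repeated measures ANOVA can give only an overall time test. It can also give contrasts and marginal means, and the article plans effect sizes. What can be said is that no baseline contrast is named.
- A reader might infer that completers will be the better-off dyads and that improvement will therefore be overstated. Section 1.0 does link carers' health to the patient's condition, so selective loss is plausible. But the article gives neither an attrition rate nor a mechanism. If dropout is unrelated to scores, only precision suffers; other mechanisms could push the estimate either way.
- A reader might take 20–30% as the expected loss of week-6 data. That holds only for independent missingness. Death or withdrawal would mostly produce monotone loss, for which the same paired rates give 11–12.5%.
- A reader might extend the point to every outcome. GP visits, LVEF and admissions have no week-6 assessment, so it does not apply to them.

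**Conclusion.** The point holds for the outcomes measured at three assessments: all carer scales, the Minnesota questionnaire and the EuroQoL questionnaire. The method the article fixes, fitted conventionally, drops observed week-6 scores of anyone missing another assessment, and its only stated target is the overall effect of time.

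Under the assumed attrition, about 11–12.5% (monotone) to 20–30% (independent) of observed week-6 data would go unused, and the standard error of the week-6 change would be 6–7% or 12–20% larger. Bias is a conditional risk, not a demonstrated fact: 0.04 to 0.10 SD at week 6 in the scenario simulated, none if dropout is unrelated to scores, and of uncertain direction otherwise. The change is worth making because a better method is readily available, but the exploratory status of these outcomes keeps the point moderate.

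**What to change.** In section 2.5.1, replace repeated measures ANOVA for the three-assessment outcomes with a likelihood-based mixed model for repeated measures, using all available assessments, with time as a factor and an unstructured covariance. Name two contrasts, week 6 minus baseline and 6 months minus baseline, each reported with a 95% confidence interval. These are the short- and long-term quantities of Objective 3, and effect sizes for the next study should be drawn from them.

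The cost is a change of wording and slightly more analysis work, in the same software and with no extra participants or visits. The model relies on data being missing at random, which may fail if loss follows events that the recorded scores do not reflect. Baseline scores of completers and non-completers should therefore be compared and reported.

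Extracting dates of patient death is not needed for this change. Because section 2.2.5 lets carers take part without their patient, such dates would cover enrolled patients only.
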